### Study Instruments

Standardized instruments adapted for female sex workers and men who have sex with men were used for the PBS and BBS. The FGD guide was standardized for all populations. All tools were available in English and Kiswahili.

### Data Entry and Management

Each study team had 2 tablets that were preloaded with customized web-based survey software (SurveyCTO) and were used for data entry and management. Data collected during PBS sessions were first compiled in hard copy format using standardized reporting forms that were filled out by the prevention officer and community researchers after PBS responses were tallied. Reporting form tallies were then entered into tablets by the prevention officers on each study team. BBS data were directly entered into tablets using SurveyCTO. Data quality checks were automated within the web-based system. Data were uploaded securely to a central server at the end of each field day via a virtual private network (VPN).

Select biological samples collected were sent to the PHDA laboratory (Table 1). These laboratory data were managed using the Laboratory Information Management Software (LMIS), uploaded to a repository in CSV format, and merged with data collected through SurveyCTO by the study’s data manager.

The study team’s qualitative researchers were responsible for digitally audio recording FGDs and transcribing and translating (into English) the FGD data.

### Data Security

Data were transmitted over an encrypted channel (HTTP secure), and personal identifiers were automatically encrypted at data entry. Access to central servers is restricted. Data will be stored in encrypted format for 5 years, following national data security protocols.

### Data Cleaning

Daily data quality checks will be performed on PBS and BBS data collected through SurveyCTO, addressing discrepancies, missing data, and inconsistencies as they are identified. The study teams’ prevention officers and site supervisors will oversee the data cleaning and quality assurance procedures.

### Data Analysis

Data from PBS and BBS will be analyzed at the group and individual levels, respectively. Descriptive statistics will be calculated, and univariate analyses will be conducted to measure previously specified outcomes (Textbox 1) and assess risk factors associated with HIV. Guided by the coverage cascade element of the effective program coverage framework [16], coverage gap analyses will be performed to identify and quantify gaps in availability coverage, contact coverage, and use coverage in relation to required coverage targets.

Thematic analysis will be done for FGD data to capture recurring concepts and ideas related to barriers and facilitators to accessing, contacting, and using prevention services that emerged during discussions.

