
### BBS Component

#### Overview

The BBS is an expansion to the standard PBS method and was led by the study teams’ clinical officers and HTS counselors. It comprised 2 data collection methods: individual, structured interviews and biological sample collection (Table 1). Importantly, in the context of this study’s objectives and research questions, data from the BBS provide critical information to describe treatment and program coverage outcomes for the study population. BBS data are only linkable to PBS data at the group level.

**Table 1 table1:** Biological samples collected from female sex workers and men who have sex with men during the biobehavioral survey in Nairobi, Kenya, from April to May 2023.

Biomarkers	Sample type	Type of test	Test location
HIV diagnosis	Capillary blood	Rapid test	Study site
Recency of HIV infection	Plasma	Laboratory-based test	PHDA^a^ laboratory
HIV-1 RNA viral load	Plasma	Laboratory-based test	PHDA laboratory
Actively taking PrEP^b^	Urine	Rapid test	Study site or in the PHDA laboratory

^a^PHDA: Partners for Health and Development in Africa.

^b^PrEP: pre-exposure prophylaxis.

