#### Individual, Face-to-Face Structured Interviews

Following the PBS, all participants who provided informed consent participated in a brief, face-to-face, structured interview with a clinical officer to gather limited demographic information, basic behavioral information related to HIV risk, and program access and service use data. These data will be linked, at the individual level, to biological samples (blood and urine), which were collected following the face-to-face interviews.

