### Participant Inclusion Criteria

To be eligible for participation in this ePBS study, female sex workers had to be assigned female at birth, aged at least 18 years, and acknowledge having received money or gifts in exchange for sexual intercourse with an individual assigned male at birth at least once in the past 3 months. Eligible men who have sex with men had to be assigned male at birth, aged at least 18 years, and report at least 1 anal sex act (insertive or receptive) with another individual assigned male at birth in the past 3 months. To be eligible, all participants had to be capable and willing to provide written or verbal informed consent to participate in the 3 components of the ePBS study, self-identify as a sex worker or a man who has sex with other men, and report actively practicing sex work or cruising within Nairobi County.

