## Results

The study enrolled 759 female sex workers (response rate: 759/769, 98.6%) and 398 men who have sex with men (response rate: 398/420, 94.7%) across 64 and 35 PBS sessions, respectively (Table 2).

In total, 758 (99.9%) female sex workers (1 participant refused participation in BBS) and 398 (100%) men who have sex with men participated in the face-to-face interview for the BBS, and all (n=1156) provided blood and urine samples for rapid tests. In total, 14.79% (171/1156) of participants (female sex workers: n=101, 59.1%; men who have sex with men: n=70, 40.9%) tested positive for HIV via rapid test. Among those testing positive, 93.6% (160/171) of participants (female sex workers: n=100, 62.5%; men who have sex with men: n=60, 37.5%) provided consent for venous blood sample collection. Three whole blood samples from female sex worker participants were discarded due to missing bar codes on the sample tubes. A total of 73 participants reported currently receiving PrEP in the BBS face-to-face interview (Table 2), and rapid urine tests were conducted on the samples from these participants (female sex workers: n=56, 77%; men who have sex with men: n=17, 23%).

**Table 2 table2:** Expanded polling booth survey (ePBS) participant enrollment and data collection among female sex workers and men who have sex with men in Nairobi County, Kenya, from April to May 2023 (n=1157).

	Female sex workers (n=759), n (%)	Men who have sex with men (n=398), n (%)
PBS participants	759 (100)	398 (100)
BBS^a^ participants	758 (99.9)	398 (100)
HIV rapid tests conducted	758 (99.9)	398 (100)
Reactive HIV rapid test results	101 (13.3)	70 (17.6)
Venous blood samples collected	100 (13.2)	60 (15.1)
Urine tests conducted	56 (7.4)	17 (4.3)

^a^BBS: behavioral and biological survey.

A total of 20 FGDs were completed with female sex workers (n=14, 70%) and men who have sex with men (n=6, 30%).

Data cleaning and analysis are ongoing. Aggregate responses from each PBS session and individual data from BBS respondents have been entered into separate data modules in the data entry software. The data will then be exported to SPSS (version 28.0; IBM Corp) for analysis. Weights will be applied to data during analyses to account for the sampling design and to adjust for unequal selection probabilities. CIs will be calculated, and descriptive analyses of the PBS and BBS data will be performed separately to address the study objectives.

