The FGD data will be simultaneously translated and transcribed into English by the qualitative study team. Qualitative notes taken during the FGDs will be incorporated into a final transcript to provide appropriate contexts and details where necessary. Thematic analysis will be used to systematically capture recurring concepts, ideas, and topics that emerged during the discussions.

Furthermore, we will use the effective program coverage framework [16] to assess gaps in availability coverage, contact coverage, and use coverage within the condom, PrEP, and antiretroviral therapy program components. Equity analyses will be conducted with program coverage data to assess inequalities in the coverage of each component intervention based on age, geography, and location typology.

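### HIV risk factors are assigned to univariate analysis; add an age-adjusted model on the BBS data, because crude associations with prevalent HIV may be confounded by age

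*Protocol article*

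**What the plan says.** Data Analysis gives one method for two tasks: "univariate analyses will be conducted to measure previously specified outcomes (Textbox 1) and assess risk factors associated with HIV". The Results section, which also describes the pending analysis, adds confidence intervals and says that "descriptive analyses of the PBS and BBS data will be performed separately to address the study objectives". The only adjustment it mentions is for the sampling: "Weights will be applied to data during analyses to account for the sampling design and to adjust for unequal selection probabilities". Such weights correct for unequal chances of selection; they do not adjust for covariates.

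On the data available, the face-to-face interview is to "gather limited demographic information, basic behavioral information related to HIV risk, and program access and service use data", and "These data will be linked, at the individual level, to biological samples (blood and urine"). Age is not named there, but Results plans equity analyses to "assess inequalities in the coverage of each component intervention based on age, geography, and location typology", so age, geography and typology must be held. Participants are "aged at least 18 years", with no upper limit. The BBS overview states that "BBS data are only linkable to PBS data at the group level".

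Limitations calls the results descriptive and not informative about causal relationships, and names recall and social desirability bias. It mentions neither confounding nor that the risk-factor estimates would be crude.

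**The concern.** The outcome is current HIV status by rapid test. It mixes recent infections with infections acquired long ago, so the chance of being positive can rise with age simply because older participants have been exposed for longer. If a behavior, a typology or contact with the program also differs by age, a univariate comparison attributes part of the age difference to that variable. A service that mainly reaches older people could then appear to go with higher HIV.

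This matters because the findings are meant to be used. The dissemination section says stakeholders can draw on them to strengthen programs and policies, and the discussion of implications says they will help refine program strategy. An association presented as a risk factor is likely to be read as a reason to act on that variable.

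**Working it through.** The article states no figure on this point, so there is none to reproduce. Three checks apply.

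**1. Is any adjusted analysis of HIV status named?** Data Analysis names univariate analysis. Results adds weights, confidence intervals and descriptive analyses. The equity analyses by age, geography and typology concern program coverage, not HIV status; they show that age is available and are not a second instance of the problem. No adjusted analysis of HIV status is named.

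**2. How large could the distortion be?** From Results: 101 of 758 female sex workers (13.3%) and 70 of 398 men who have sex with men (17.6%) tested positive. Assumed, because the article gives nothing: half of each sample is older, the age–HIV odds ratio is 2 to 4, and an exposure with no effect of its own is present in 60% of older and 40% of younger participants (moderate imbalance) or in 70% and 30% (strong imbalance).

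Let p_y and p_o be prevalence in younger and older participants, chosen so that (p_y + p_o)/2 equals the observed prevalence and their odds ratio equals the assumed one. With exposure share e in the older half and 1 − e in the younger half:

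- prevalence if exposed = e·p_o + (1 − e)·p_y
- prevalence if unexposed = (1 − e)·p_o + e·p_y
- crude OR = odds if exposed ÷ odds if unexposed

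Female sex workers, low end (age OR 2, e = 0.6): p_y = 0.0942, p_o = 0.1722. Exposed 0.6 × 0.1722 + 0.4 × 0.0942 = 0.1410; unexposed 0.4 × 0.1722 + 0.6 × 0.0942 = 0.1254. Crude OR = (0.1410/0.8590)/(0.1254/0.8746) = 1.14.

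High end (age OR 4, e = 0.7): p_y = 0.0608, p_o = 0.2057. Exposed 0.1622, unexposed 0.1043. Crude OR = (0.1622/0.8378)/(0.1043/0.8957) = 1.66.

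| Age–HIV OR | FSW 60/40 | FSW 70/30 | MSM 60/40 | MSM 70/30 |
|---|---|---|---|---|
| 1 | 1.00 | 1.00 | 1.00 | 1.00 |
| 2 | 1.14 | 1.31 | 1.15 | 1.31 |
| 3 | 1.23 | 1.52 | 1.23 | 1.52 |
| 4 | 1.29 | 1.66 | 1.29 | 1.67 |

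(FSW: female sex workers; MSM: men who have sex with men.) If exposure is equally common at both ages, the crude OR is 1.00 in every row.

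A harsher illustration gives a similar upper value. Take prevalence 8% in the younger 55% and 20% in the older 45%, with exposure in 20% and 70%. Exposed: (0.11 × 0.08 + 0.315 × 0.20)/0.425 = 0.169. Unexposed: (0.44 × 0.08 + 0.135 × 0.20)/0.575 = 0.108. Crude OR 1.68. This needs an age–exposure OR of (0.7/0.3)/(0.2/0.8) = 9.3, a very strong link.

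**3. Can the data carry an adjusted model?** At 10 positives per parameter, 101/10 gives about 10 parameters for female sex workers and 70/10 gives 7 for men who have sex with men. At 20 per parameter the counts are about 5 and 3. Clustering lowers these. There is one session per location, so positives average 101/64 = 1.6 and 70/35 = 2.0 per location, and typology and subcounty do not vary within a location. Age plus a few typology categories is realistic; all 12 subcounties are not.

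**The case against.** The strongest reply has four parts.

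First, naming univariate analysis does not exclude more, and an article may leave model details to an analysis plan that is not shown. A reader might infer that the plan rules out adjustment; the text does not say so. The point still stands, because the article does name a method for this aim, and that method does not suit it. If an adjusted model exists elsewhere, the published description needs correcting.

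Second, risk factors belong to none of the three objectives or four research questions, and the study calls itself descriptive. This stands, and it makes the point secondary. For describing where the burden lies, crude prevalence by group is legitimate. But the clause speaks of risk factors, and the caveat on causality does not tell readers that the associations are unadjusted.

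Third, a reader might infer that age will confound the results, or that programs would be misdirected. The documents support neither: they give no age–HIV or age–exposure figure, and the distortion vanishes if either link is absent. A reader might also think that time at risk, such as years in sex work, could be adjusted for. Nothing in the article shows that it is collected.

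Fourth, age adjustment does not cure reverse direction. Testing, program contact and condom use can change after a diagnosis. This stands and shapes the remedy. So does the limit on PBS items, which cannot be adjusted for an individual's age.

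**Conclusion.** The point holds in a limited form. Univariate analysis is the method named for assessing risk factors for prevalent HIV, and no adjusted analysis is named. Crude associations may be confounded by age. The size is unknown: a null exposure would show a crude odds ratio of about 1.1 to 1.7 if age is related to HIV with an odds ratio of 2 to 4 and the exposure is moderately to strongly unbalanced by age, and 1.0 if either relation is absent. Those inputs are assumptions. The conclusion also rests on age being recorded in the BBS, which the planned equity analyses imply but the interview description does not state. Prevalence estimates, outcome estimates and coverage analyses are not affected.

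**What to change.** For variables collected in the BBS, and separately for each key population, add a survey-weighted logistic or modified Poisson model for HIV status, with clustering by location. Adjust for age and, where the number of positives allows, for a collapsed location typology. Then:

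- report crude and adjusted estimates side by side;
- do not interpret as risk factors any variables that can follow from an HIV diagnosis, such as PrEP or antiretroviral therapy use;
- label associations that rest on PBS items as crude;
- add residual confounding and reverse direction to Limitations.

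The article describes cleaning and analysis as ongoing, and the change needs no new data. The cost is a little more analysis work and wider intervals for the adjusted estimates, more so for men who have sex with men, with 70 positives over 35 locations.

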### Knowledge Translation and Dissemination

The study’s findings and lessons on the feasibility and utility of ePBS as a data collection method will be shared through participation in the Nairobi County Key Population Technical Working Group and the National Key Population Technical Working Group led by the NASCOP. This working group comprises members representing implementing partners, key population community representatives, donors, and the Kenyan Ministry of Health officials. These stakeholders will have the opportunity to use the study’s findings to inform and strengthen programs and policies for key populations in Nairobi. In addition, the study results will be shared with the PHDA-SWOP Community Advisory Board and peer educators. These insights will support the development of strategies to enhance program effectiveness and improvement.

Research findings and methodological insights from implementing the novel ePBS study will be shared with academic communities in Kenya and globally through international conferences and peer-reviewed journal articles. PHDA is a part of an extensive, existing network of researchers in public health sciences, health policy, and basic and natural sciences who focus on HIV and sexually transmitted infections. Other scientific forums within the University of Manitoba will be leveraged to share the findings.

## Results

The study enrolled 759 female sex workers (response rate: 759/769, 98.6%) and 398 men who have sex with men (response rate: 398/420, 94.7%) across 64 and 35 PBS sessions, respectively (Table 2).

In total, 758 (99.9%) female sex workers (1 participant refused participation in BBS) and 398 (100%) men who have sex with men participated in the face-to-face interview for the BBS, and all (n=1156) provided blood and urine samples for rapid tests. In total, 14.79% (171/1156) of participants (female sex workers: n=101, 59.1%; men who have sex with men: n=70, 40.9%) tested positive for HIV via rapid test. Among those testing positive, 93.6% (160/171) of participants (female sex workers: n=100, 62.5%; men who have sex with men: n=60, 37.5%) provided consent for venous blood sample collection. Three whole blood samples from female sex worker participants were discarded due to missing bar codes on the sample tubes. A total of 73 participants reported currently receiving PrEP in the BBS face-to-face interview (Table 2), and rapid urine tests were conducted on the samples from these participants (female sex workers: n=56, 77%; men who have sex with men: n=17, 23%).

**Table 2 table2:** Expanded polling booth survey (ePBS) participant enrollment and data collection among female sex workers and men who have sex with men in Nairobi County, Kenya, from April to May 2023 (n=1157).

	Female sex workers (n=759), n (%)	Men who have sex with men (n=398), n (%)
PBS participants	759 (100)	398 (100)
BBS^a^ participants	758 (99.9)	398 (100)
HIV rapid tests conducted	758 (99.9)	398 (100)
Reactive HIV rapid test results	101 (13.3)	70 (17.6)
Venous blood samples collected	100 (13.2)	60 (15.1)
Urine tests conducted	56 (7.4)	17 (4.3)

^a^BBS: behavioral and biological survey.

A total of 20 FGDs were completed with female sex workers (n=14, 70%) and men who have sex with men (n=6, 30%).

Data cleaning and analysis are ongoing. Aggregate responses from each PBS session and individual data from BBS respondents have been entered into separate data modules in the data entry software. The data will then be exported to SPSS (version 28.0; IBM Corp) for analysis. Weights will be applied to data during analyses to account for the sampling design and to adjust for unequal selection probabilities. CIs will be calculated, and descriptive analyses of the PBS and BBS data will be performed separately to address the study objectives.

The FGD data will be simultaneously translated and transcribed into English by the qualitative study team. Qualitative notes taken during the FGDs will be incorporated into a final transcript to provide appropriate contexts and details where necessary. Thematic analysis will be used to systematically capture recurring concepts, ideas, and topics that emerged during the discussions.

Furthermore, we will use the effective program coverage framework [16] to assess gaps in availability coverage, contact coverage, and use coverage within the condom, PrEP, and antiretroviral therapy program components. Equity analyses will be conducted with program coverage data to assess inequalities in the coverage of each component intervention based on age, geography, and location typology.

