### Target Sample Size Calculation

To be representative of each key population group, the study’s sampling strategy was based on probability sampling techniques that provided an equal chance to all members of the study populations, meeting defined inclusion criteria, to be included in the study. The determination of an appropriate sample size for a single study domain is usually based on the following considerations: (1) the number of measurement units in the population, (2) the parameter of interest, and (3) the degree of confidence by which the parameter is estimated and the desired level of precision.

One objective of our study was to estimate the HIV prevalence and incidence among female sex workers and men who have sex with men in Nairobi County. As such, sampling parameters were set with the prevalence and sample size having 95% statistical confidence, with a desired precision of +5% or –5%.

The sample size for PBS and BBS study was calculated using the following formula: *n* = [1.96^2^*p*(1 – *p*)(*DEFF*)]/*d*^2^. Where *p* is HIV prevalence, *DEFF* is the design effect of the sampling approach, and *d* is the desired precision.

The finite population correction factor is then applied to the derived sample size using the following formula: *nf* = (*n **
*N*)/[(*n* + (*n* – 1)]. Where *nf* is the sample size adjusted for finite population correction, *n* is the sample size required, and *N* is the population size.

To calculate the sample size for this ePBS study, we used the most recent estimate of HIV prevalence among female sex workers (26%) and men who have sex with men (12%) in Nairobi, as reported in a 2017 study conducted by NASCOP [7]. The sample size calculation was adjusted to accommodate an anticipated nonresponse rate of 15%. The final target sample size, adjusted for population size and nonresponse, for female sex workers was n=769 and for men who have sex with men was n=420. Ideally, each PBS session comprises 10 to 12 participants; the total target sample sizes for female sex workers and men who have sex with men were divided by 12 to determine the total number of PBS sessions required for each key population group, that is, 64 PBS sessions with female sex workers and 35 sessions with men who have sex with men.

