#### Stage 1 Sampling

As a first step, the ePBS study team developed the sampling frame by validating lists of mapped locations in Nairobi County where female sex workers and men who have sex with men solicit clients, cruise, meet sexual partners, and engage in sexual activities. The sample frame was derived from a programmatic mapping exercise conducted in 2018 [6]. The lists were updated—that is, closed locations were removed and newly emerged locations were added—through a validation process facilitated by the study team members who are in regular, direct contact with key population members. Through this validation process, population size estimates for each location, the days and times when these locations are operational, and the days when the locations have the highest number of female sex workers or men who have sex with men were verified and revised, as needed, via a standardized approach.

The lists of validated locations (1 each for female sex workers and men who have sex with men) formed the sampling frames representing the universe of locations across Nairobi County. Key population members spending time within a given location tend to be more homogeneous, in terms of typology and risk behavior, than those in different locations [27]. As such, potential participants for each PBS session were randomly selected from a single location. During the first stage of sampling, 99 locations (equal to the number of PBS sessions planned for each group) were randomly selected such that 1 PBS session was conducted per selected location. The random selection of key population group–specific locations from which potential participants were identified was stratified by subcounty and location typology.

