#### Stage 2 Sampling

In stage 2 of sampling, each of the 99 randomly selected locations was randomly allocated to an assigned week and day on which potential participants were enrolled from the location. For example, data collection for this ePBS study was projected to take 30 days; for each location, 1 week (ie, from weeks 1 to 4 of the study period) was randomly selected first, followed by the random selection of 1 specific day within that chosen week. This process determined the precise week and day that each selected location was designated for the study. Ultimately, 10 to 12 potential participants were randomly approached by community researchers at the location on the specified day and week and invited to take part in the study.

This 2-stage sampling approach ensured that participants were representative of the total population of the key population group by geography (subcounty) and location typology across days of the week, yielding a comprehensive and diverse sample of participants from communities of female sex workers and men who have sex with men in Nairobi County.

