### Participant Enrollment and Data Collection Site Preparation

Potential participant enrollment occurred at selected locations on the allocated days of the week, according to the study’s sampling frame. Enrollment primarily occurred in the late afternoon or evening on the day of data collection to increase the likelihood of meeting a higher number of female sex workers or men who have sex with men in the location. Peer educators and outreach workers from the SWOP clinics facilitated the identification of potential participants within their own key population group. They were responsible for introducing potential participants to the study and assessing their eligibility. Any eligible individuals were provided with detailed information about ePBS. If eligible participants were interested in participating in the study, they were brought to the data collection site by peer educators and outreach workers. As much as possible, data collection occurred within the selected locations. Ahead of participant enrollment, the study team members scouted selected sites to identify suitable spaces for safe and confidential data collection. Team members were responsible for setting up stations for PBS and private, quiet locations for face-to-face structured interviews and biological sample collection. If the selected sites posed challenges (eg, logistical or safety challenges) for data collection, prescouted alternate locations nearby were used instead.

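### Sampling people present on one random day per location gives inclusion chances that rise with attendance; the equal-chance and total-population claims do not follow, and PBS tallies can be weighted only by session

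*Protocol article*

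**What the plan says.** Stage 1 Sampling draws 99 locations (64 for female sex workers, 35 for men who have sex with men), stratified by subcounty and typology; they "were randomly selected such that 1 PBS session was conducted per selected location". Stage 2 Sampling gives each location one random week and then one random day, on which 10 to 12 of the people there are approached. On timing, "Enrollment primarily occurred in the late afternoon or evening" (Participant Enrollment and Data Collection Site Preparation).

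Three statements describe what this achieves:

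- Target Sample Size Calculation: the strategy "provided an equal chance to all members of the study populations, meeting defined inclusion criteria, to be included in the study".
- Stage 2 Sampling: "This 2-stage sampling approach ensured that participants were representative of the total population of the key population group by geography (subcounty) and location typology". The sentence goes on to add days of the week.
- Results: "Weights will be applied to data during analyses to account for the sampling design and to adjust for unequal selection probabilities". The components of the weights are not named.

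The two quantitative parts differ in what a weight can attach to. PBS answers are anonymous and unlinked, tallied per session and analyzed by group; "BBS data are only linkable to PBS data at the group level" (BBS Component, Overview). BBS data are individual, carry a unique code, and are the stated source for treatment and program coverage outcomes. The interview is described in one sentence, as intended "to gather limited demographic information, basic behavioral information related to HIV risk, and program access and service use data". Limitations does not mention attendance.

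**The concern.** People can be selected only while present at a sampled location on its sampled day. Someone there most days has more chances than someone there once a week. Eligibility requires a qualifying act in the past 3 months, self-identification and active sex work or cruising in the county, which still allows attendance to vary. This inequality is between persons. It is separate from the probability of drawing a location and from the fixed take per location, and it remains when both are corrected.

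If contact with the program, testing, violence or HIV status varies with attendance, an estimate without an attendance correction describes the population weighted by attendance, while the article presents it as describing all members. The planned equity analyses (age, geography, location typology) would not show such a difference directly. The results are meant to guide county and national programs, and the method is being piloted for wider use, so the population to which the estimates refer matters.

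**Working it through.** **1. What the location-day weight leaves behind.** Let π(j) be the chance that location j is drawn, 1/D the chance of a given day, and m/M the chance of being approached among the M people present. The weight that fully corrects these stages is 1/[π(j) × (1/D) × (m/M)]. Person i can be drawn on each location-day that he or she attends, and each contributes an expected weight of 1. The expected total weight of person i is therefore a(i), the number of location-days attended. The weighted proportion estimates Σ a(i)y(i) / Σ a(i), which equals the population proportion only if attendance and outcome are uncorrelated. Equal chance would require the same a(i) for everyone.

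**2. Size.** The article has no attendance figure to reproduce. Assumption: half the population attends l days a week (1 or 2) and half h days (3 or 5).

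- Sample share of frequent attenders: s = h/(h + l), against 0.50 in the population.
- Bias in a proportion: (s − 0.50) × (outcome among frequent minus outcome among infrequent attenders).
- Kish factor for inverse-attendance weights: K = (h + l)²/(4hl); confidence intervals widen by √K.

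| Days (h vs l) | s | Bias, 10-point gap | 20-point gap | 30-point gap | K | √K |
|---|---|---|---|---|---|---|
| 3 vs 2 | 0.600 | 1.0 | 2.0 | 3.0 | 25/24 = 1.04 | 1.02 |
| 5 vs 2 | 0.714 | 2.1 | 4.3 | 6.4 | 49/40 = 1.23 | 1.11 |
| 3 vs 1 | 0.750 | 2.5 | 5.0 | 7.5 | 16/12 = 1.33 | 1.15 |
| 5 vs 1 | 0.833 | 3.3 | 6.7 | 10.0 | 36/20 = 1.80 | 1.34 |

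With a gap of 0 the bias is 0 in every row. The sign follows the sign of the gap, which the article does not give. The article's ±5 points was set for HIV prevalence, so for other outcomes it is only a yardstick.

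**3. Which part can be corrected.**

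- PBS: cards are not tied to persons, so every card in a session carries the same weight. A session factor can shift weight between sessions but cannot undo over-representation of frequent attenders within one. No analysis plan can change this.
- BBS: each record has a person code, so a weight of 1/a(i) can be applied if attendance was recorded. The interview summary names no such item, but it lists broad categories only, and the instruments mentioned under Study Instruments are not shown.

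**4. Internal consistency.** A design that gave every eligible member the same chance would need no adjustment for unequal selection probabilities. The sentences in Target Sample Size Calculation and Results therefore conflict, whatever the weights turn out to contain.

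**The case against.** The strongest reply is that an article need not list weight components or questionnaire items. The planned weights may include attendance, and the behavioral part of the interview may ask about days or places worked. This stands for the BBS: that attendance is not described does not show that it was not collected. It does not rescue the equal-chance sentence, which states a property that the design lacks, and it cannot help the PBS.

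A second reply is that the representativeness sentence is limited to geography, typology and days of the week. That is a fair reading, but none of these covers how often a person attends.

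Three stronger readings are tempting and are not supported:

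- A reader might infer that the estimates describe frequent attenders instead of the whole population. Occasional attenders are under-represented, not excluded.
- A reader might infer that program coverage is overstated. Frequent attenders may well meet peer educators more often, but the article has no data on this, so the direction is not established.
- A reader might infer that unlinked cards make coverage and HIV estimates uncorrectable. The article places treatment and program coverage, as well as the biological results, in the BBS, where a person-level weight is possible.

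**Conclusion.** The point holds in a limited form. Inclusion chance rises with location-days attended, so the equal-chance statement is wrong as written, conflicts with the planned weighting, and leaves representativeness of the total population unsupported with respect to attendance. PBS estimates refer to the attendance-weighted population at mapped locations, and no weighting scheme can correct this within a session. BBS estimates share the problem unless attendance was asked and is used.

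The size rests wholly on the assumed equal split and attendance of 1-2 against 3-5 days a week: 60-83% frequent attenders instead of 50%, and 1.0-3.3 points of bias per 10-point outcome gap, down to none where outcome and attendance are unrelated. People who never use mapped locations are a separate question of frame coverage, which attendance weights do not address.

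**What to change.** 1. **BBS.** State whether the weights include attendance. If an item on days attended or number of locations used exists, multiply the location-day weight by trimmed inverse attendance and report estimates with and without it. Cost: one further weighted run, with confidence intervals about 2-34% wider in the scenarios above.
2. **PBS.** State that weights are session-level only and that estimates refer to the attendance-weighted population at mapped locations. A session factor from the mean inverse attendance of the same group's BBS is at most a sensitivity analysis, reported with the caveat that within-session bias remains.
3. **Wording.** Replace the equal-chance sentence in Target Sample Size Calculation. In Stage 2 Sampling, restate the inference population as people present at mapped locations on the sampled days and times, attendance-weighted unless corrected. Add under-representation of occasional attenders to Limitations.

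No new data are needed. Analysis is described as ongoing, so the changes can still be made. If no attendance item was collected, only the PBS statement in item 2 and the wording in item 3 apply, and the restated population then covers the BBS as well.
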